### Variables and research tools

Specific research tools for each objective are summarized in Table 2, which includes corresponding variables as well as the sources that will be used to obtain required data and the time of data collection.

**Table 2 Tab2:** Summary of methodology and approach

Variables	Sources	Time of data collection	
		CHUS-RCT	Comparison fertility clinics
1. Development and implementation of the interdisciplinary lifestyle intervention			
Health professionals’ perceptions and satisfaction toward obesity and fertility management	Questionnaire	At the end of the study	Retrospectively
	Focus groups		
Patients’ perceptions and satisfaction toward weight management and fertility care	Questionnaire	At 18 months or 24–28 weeks pregnant	At the end of the study
	Focus groups		
2. Evaluation of lifestyle benefits and impact on fertility, pregnancy complications and neonatal outcomes			
Live-birth rate	Review of patient medical record	Throughout the study	Retrospectively
Lifestyle and anthropometric outcomes^a^		Baseline, 6 months, 12 months, and 18 months. Among women who become pregnant: beginning of the pregnancy and 24–28 weeks pregnant.	N/A
∙ *Anthropometric measures*	Standard calibrated scale and standing electric bioimpedance		
∙ *Vital signs*	Automatic blood pressure monitor		
∙ *Metabolic markers related to insulin secretion, androgen, lipid profile and OGTT*	Blood sample		
∙*Lifestyle habits (diet, exercise, sleep, alcohol, and tobacco)*	Questionnaire adapted from the one used by Statistics Canada for the latest Canadian Health Survey		
∙ *Physical fitness level*	Six-minute walk test		
∙ *Daily energy expenditure from physical activities, time spent in various physical activity intensities and step count*	Tri-axial accelerometer		
∙ *Readiness for change*	Questionnaire (WLRT [75])		
∙ *Quality of life*	Questionnaire (FertiQoL [76])		
Fertility outcomes		Throughout the study	Retrospectively
∙ *Pregnancy rate*	Positive β-hCG level in the serum		
∙ *Others*	Review of patient medical record		
Pregnancy adverse outcomes	Review of patient medical record	Throughout the study	Retrospectively
Neonatal outcomes	Review of patient medical record	Throughout the study	Retrospectively
3. Evaluation of cost per live birth/cost-effectiveness of the interdisciplinary lifestyle intervention			
Costs of the interdisciplinary lifestyle intervention^a^	Questionnaires	Throughout the intervention	N/A
	Administrative data		
Costs of fertility treatments	Review of patient medical record	Throughout the study	Retrospectively
	Questionnaires		
	Administrative data		
Costs of adverse events or complications	Review of patient medical record	Throughout the study	Retrospectively
	Questionnaires		
	Administrative data		
4. Knowledge transfer			
Scientific meeting presentations	ASRM, CSEM, ENDO and other annual meetings	Throughout the study	
Publication in scientific journals	Human reproduction, Fertility and sterility, Journal of clinical endocrinology & metabolism, etc.	Throughout the study	
Presentations to decision-makers and knowledge users	Solicited and unsolicited invitations	Throughout the study	
Diffusion to stakeholders	Conduit, letters, e-mails	Throughout the study	
Executive summary		At the end of the study	

*ART* Assisted reproductive technologies, *β-hCG* Beta-human chorionic gonadotropin, *IVF In Vitro* Fertilization, *ASRM* American society for reproductive medicine, *CSEM* Canadian society of endocrinology and metabolism, *ENDO* Endocrine society, *FertiQoL* Fertility quality of life tool, *OGTT* Oral glucose tolerance test, *WLRT* Weight loss readiness tool

^a^CHUS-RCT: *Centre hospitalier universitaire de Sherbrooke*-randomized controlled trial

#### Health professionals’ perceptions and satisfaction (Objective 1)

Health professionals’ attitudes, perceptions, self-efficacy toward obesity management, and other characteristics (age, experience in obesity management) will be evaluated with a questionnaire that we have developed and used in previous studies [55]. Self-efficacy is defined as the set of beliefs about one’s capabilities to perform at a designated level. It is particularly important in the context of the implementation of a new program since it may be influenced by the practice environment [56]. For health professionals to engage in weight management with their patients, they must not only accept this as part of their role but also feel that they are competent to accomplish the task. Negative attitudes toward obese individuals and perceptions to the effect that available treatments are ineffective can prevent the engagement of health professionals in weight management. There is also a positive correlation between the feeling of competency and the degree of engagement regarding various aspects of obesity management and improved attitude towards obese individuals [57, 58]. A separate questionnaire will gather detailed information on strengths of the program, difficulties and areas of possible improvement.

A qualitative in-depth analysis of key stakeholder perceptions of the program and fertility clinics will be performed using semi-structured interviews (MDs, nurses, dietitians, kinesiologists, psychologists, clinic administrative personnel and directors), as we have previously done [59, 60]. This will increase our understanding of their personal experience, inter-professional collaboration and satisfaction with the program, and further identify and detail strengths and areas for potential improvement. This will also permit a better understanding of the change process.

#### Patients’ perceptions and satisfaction (Objective 1)

Patient expectations and perceptions of their personal experience regarding weight management, fertility care and pregnancy follow-up, as well as their satisfaction regarding management by their health professionals will be evaluated with questionnaires based on experience from previous studies. A qualitative in-depth analysis of patients’ perceptions of the program and medical care will also enhance our understanding of their personal experience with the program. After the completion of the quantitative evaluation of impact of the program on patients, a theoretical sample based on the technique of critical incidents will be used to create a sub-sample of the whole group. Twenty patients will be recruited in each of the 4 participating clinics (80 patients). To be recruited those patients will have to show certain characteristics (different levels of satisfaction with their care (at CHUS, based on questionnaires), different fertility or pregnancy outcomes, loss or gain of weight during follow-up, etc.). The patients will be participating in a taped-recorded semi-structured qualitative interview to assess their perceptions of impact of their participation into the program (continuity of care, perceptions of changes, contribution to change, quality of life, perspectives of future changes, explanation of level of satisfaction with the program). An interview guide with open-ended questions adapted from the principal variables of the study, the Diabetic Empowerment Scale (DES) [59], and the Impact of Weight on Quality of Life (IWQOL-lite) questionnaire [61] will be used as done in previous studies from members of our group [49, 62].

#### Evaluation of anthropometric and lifestyle benefits and impact on fertility, pregnancy and neonatal outcomes (CHUS only) (Objective 2)

Evaluations of anthropometric measures and lifestyle habits will take place at baseline, prior to randomisation, and then every 6 months for 18 months. Among women who become pregnant, data will be collected, at the beginning of the pregnancy and at 24–28 weeks. If a woman becomes pregnant within a month of a standard evaluation visit, this visit will be considered as the first pregnancy visit. If a miscarriage occurs, the original follow-up will continue until 18 months or the end of another pregnancy. An overview of the study design and data collection is provided in Fig. 1.

**Fig. 1 Fig1:**
[figure not shown]
Summary of design and data collection of the Obesity-Fertility protocol

##### Anthropometric measures and vital signs:

Weight will be measured by a standard calibrated scale and height will be measured with a stadiometer. In non-pregnant women, waist circumference will be measured with a measuring tape, as recommended [47, 63]. Fat mass and percent body fat will be measured by standing electric bioimpedance, which was shown to be reliable compared to underwater weighing and supine tetrapolar bioimpedance [64, 65]. Blood pressure and pulse rate will be measured after five minutes of rest, in the sitting position. The average of two measurements will be used for analysis.

##### Blood sample:

Different metabolic markers related to insulin secretion, androgen and lipid profile will be measured fasting: apolipoprotein B (ApoB), total cholesterol, triglycerides, high-density lipoprotein cholesterol (HDL), low-density lipoprotein cholesterol (LDL), cholesterol ratio, thyroid-stimulating hormone (TSH), prolactin (PRL), cortisol, adrenocorticotropic hormone (ACTH), β-hCG, total and free testosterone, Sex hormone-binding globulin (SHBG), 17-hydroxyprogesterone, dehydroepiandrosterone sulfate (DHEAS), androstenedione, C-peptide, glucose and insulin. A 2-hour oral glucose tolerance test (OGTT) will be also performed with blood sample taken every 30 min. Samples will be stored at each time points for future measurements of adipokines or other analytes pertinent to the objectives of this study, if funding allows it.

##### Lifestyle:

Physical activity level and eating habits will be measured using a questionnaire adapted from the one used by Statistics Canada for the latest Canadian Health Survey. This questionnaire inquires about the frequency and duration of active travelling, leisure time, and sedentary activities (television watching, video games, computers). We chose this questionnaire since it allows comparison of the characteristics of our patients to those of the general Canadian population. Moreover, women will be asked to wear a tri-axial accelerometer (GT3X+, Actigraph, Pensacola, FL, USA) on their hip for seven consecutive days except during sleep and showering/bathing. The accelerometer will be used to estimate daily energy expenditure from physical activities, time spent in various physical activity intensities and step count. The GT3X+ has been shown to be a valid and reliable measure of physical activity in free living conditions [66].

##### Fitness level:

The six-minute walk test (6MWT) is a simple test that has been used to estimate functional capacity in obese subjects and is also a predictor of morbidity and mortality [67–69]. The 6MWT will be performed according to the protocol recommended by the American Thoracic Society in a 20-meter hallway marked every 5 m with coloured tapes on the floor, and measures the distance that a patient can quickly walk in a period of 6 min [70]. It has been shown that weight loss increases fitness level early in the weight loss process, making this test a very accurate tool to evaluate the impact of the intervention on obese or overweight patients’ functional capacity [71–73].

##### Readiness for change:

In the course of previous prospective studies, we have designed a 22-question weight loss readiness tool (WLRT) questionnaire based on Prochaska and DiClemente’s Stages of Change Model [47, 74]. It evaluates the motivational readiness of patients regarding weight management, nutrition and physical activity, and could predict response to an intervention. Our WLRT takes 5–10 min to fill out, making it a clinically applicable tool. It has been useful to identify subjects with greater chances of success for lifestyle modification in a previous pilot study [75]. Its predictive value will be assessed in this study, but it will also serve to explore the mechanisms of potential benefits of our intervention and for stratified analyses.

##### Quality of life:

The impact of fertility problems and its treatment on quality of life will be measured using the fertility quality of life (FertiQoL) tool, a reliable and sensitive questionnaire to evaluate quality of life in individuals with fertility problems [76].

#### Evaluation of fertility, pregnancy complications and neonatal outcomes (all sites)

##### Medical records:

Chart review of the mother will be performed using a standardized evaluation grid, and we will check personal medical and surgical history, medications, weight, and any particular events at each visit. This chart review will also identify information about fertility treatments and pregnancy complications. Information about the newborn will be collected *via* the obstetric file of the mother.

##### Administrative data and other databases:

Data from the chart review will be cross-validated with administrative data and any databases used in fertility clinics and/or local hospitals. At the CHUS, all laboratory testing and all information regarding hospitalisations are merged together and kept in the “*Centre informatisé de recherche évaluative en services et soins de santé”* (CIRESSS) database, which is available for research with appropriate authorizations.

### Data analyses and interpretation

For objectives 1–2, all comparisons between randomized groups at the CHUS will follow both the intent-to-treat and/or per-protocol principles, and will consider results at the end of study. For repeated measures, the last-observation-carried-forward method will be used for women who drop out or become pregnant (depending on analyses). Time-to-event analyses will also be performed for fertility outcomes, with censoring for drop out alone, as well as for anthropometric outcomes, with censoring for both drop out and occurrence of pregnancy. Univariate analyses will compare the change in a variable in the intervention group with the change in this variable in the control group, using two-tailed unpaired *t* tests (for continuous variables) and chi-square or Fisher’s exact tests (for categorical variables). Changes in weight will also be compared for the same follow-up duration with changes for women seen at the other fertility clinics, using ANOVA tests. For the other variables, only end-of-study comparisons will be performed between the two groups in Sherbrooke and the three other fertility clinics, using ANOVA tests (for continuous variables) and logistic regressions (for categorical variables). Bonferroni-corrected p-values will be performed to adjust for the multiplicity of comparisons and an α level of 5 % will be considered significant for all analyses. Continuous variables that are not normally distributed will be log-transformed in order to ascertain normal distribution. Multivariate analyses will also be used in order to adjust for baseline differences and for potential confounders, and to determine independent predictors of outcomes. Triangulation will be performed between quantitative and qualitative data.

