### Intervention

#### Control arm

Participants assigned to the control group will receive standard fertility treatments, which will be initiated as soon as clinically indicated. Standard fertility treatments may include lifestyle counselling by the obstetrician-gynecologist certified in gynecologic reproductive endocrinology and infertility (GREI), reproductive endocrinologist or fertility specialist in charge of the care of the patient.

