#### Intervention arm

Participants allocated to the intervention group will be invited to participate in the interdisciplinary lifestyle intervention and will have to delay other fertility treatments for six months. After 6 months of lifestyle intervention alone, women who are not pregnant will begin pharmacologic fertility treatments, as indicated, in conjunction with the lifestyle intervention that will continue to be offered. The aim of the intervention will be to implement progressive and sustainable lifestyle changes in order to reach a modest weight loss. Women will be invited to individually meet with a dietitian and a kinesiologist (20–30 min each) at 0, 3, 6 weeks and then every 6 weeks over a period of 18 months or until the end of pregnancy. A follow-up phone call/email will also take place once between each meeting for additional support. The dietitian will use 3-day food records to evaluate the women’s food intake throughout the program. To help improve patient’s diet, Canada’s Food Guide and the “Healthy Plate” [51] will be the main tools use for nutritional counselling. The kinesiologist will be responsible for taking anthropometric measures and vital signs and for coaching women to increase their physical activity level. A pedometer will be offered to assist the patient. Patients will be guided by the dietitian and the kinesiologist to formulate S.M.A.R.T goals (specific, measurable, attainable, realistic, and timely) at each meeting. The members of our interdisciplinary team will be trained in motivational interviewing. This training can positively affect the attitude to behaviour change in obese infertile women [52].

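### Carrying the last value forward for women who conceive or drop out biases the secondary weight and lifestyle comparison, in a direction and by an amount the protocol does not fix

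*Protocol article*

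**What the plan says.** All references are to the protocol article.

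- **Missing values.** Data analyses and interpretation says that "the last-observation-carried-forward method will be used for women who drop out or become pregnant", and adds in parentheses that this depends on the analysis. It does not say which analyses are meant, or which value is carried.
- **Comparison.** The same section says that randomised comparisons "will consider results at the end of study". Change in continuous variables is compared between arms by a two-sided unpaired t test.
- **Second analysis.** Time-to-event analyses are planned for fertility outcomes, "as well as for anthropometric outcomes, with censoring for both drop out and occurrence of pregnancy".
- **Treatment start.** Control women receive "standard fertility treatments, which will be initiated as soon as clinically indicated" (Control arm). Intervention women "will have to delay other fertility treatments for six months" (Intervention arm).
- **Visits.** Anthropometric and lifestyle measures are taken at baseline, 6, 12 and 18 months. Women who conceive are also measured at the beginning of pregnancy and at 24–28 weeks (Objective 2 evaluation section and Table 2).
- **Link to the outcome.** The Background says that a loss of 5–10 % of body weight can restore ovulation. It cites an earlier randomised trial with losses of 4.7 versus 1.3 kg and 18-month pregnancy rates of 61 versus 21 %.

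**The concern.** Pregnancy is the aim of the trial, so the carry-forward rule will apply to many women. The design makes the arms differ in when conception is likely. If the last scheduled visit is the value carried, a woman who conceives before month 6 enters the 18-month comparison with a change of zero. One who conceives between months 6 and 12 enters with her 6-month change. The mix of zeros, 6-month and 12-month values then differs by arm, even if the programme does nothing to weight. If weight loss also brings conception forward, the timing of the carried value depends on the outcome itself.

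At stake is the first-listed category of secondary outcomes, and with it the evidence that the programme achieves the modest weight loss it aims for. An end-of-study difference would partly measure who conceived when.

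**Working it through.** The protocol gives no figure for the weight comparison and none for conception rates, so there is nothing to reproduce. What follows illustrates the mechanism under stated assumptions. The reference value is the 18-month change had neither pregnancy nor dropout occurred.

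**From the documents:** visits at 0, 6, 12 and 18 months; 10 % dropout; 58 women per group; losses of 4.7 and 1.3 kg in the cited trial.

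**Assumed:** monthly conception hazards, weight paths, dropout spread evenly over 18 months, and an SD of change of 4.5 kg.

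**Formulas.** With H(t) the cumulative conception hazard, the share still observed at month t is S(t) = exp(−H(t)) × (1 − 0.10·t/18). With mean changes m6, m12 and m18, the carried-forward mean at month 18 is m6·[S(6) − S(12)] + m12·[S(12) − S(18)] + m18·S(18). The share with baseline carried throughout is 1 − S(6).

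**1. Identical paths in both arms (−3, −4, −4.5 kg), conception unrelated to weight.**
- Control, 3 % per month: S = 0.8074, 0.6512, 0.5245. Baseline is carried for 19 %. Mean = −3(0.1562) − 4(0.1267) − 4.5(0.5245) = −3.34 kg.
- Intervention, 1 % per month to month 6, then 3 %: S = 0.9104, 0.7342, 0.5913. Baseline is carried for 9 %. Mean = −3(0.1762) − 4(0.1429) − 4.5(0.5913) = −3.76 kg.
- The spurious difference is 0.42 kg in favour of the programme. With 3 % in both arms throughout it is zero, so the timing difference between arms is its cause.
- With control hazard k, and k/3 then k in the intervention arm:

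| k per month | last scheduled visit carried | beginning-of-pregnancy value carried |
|---|---|---|
| 2 % | 0.30 kg | 0.20 kg |
| 3 % | 0.42 kg | 0.29 kg |
| 4 % | 0.53 kg | 0.36 kg |
| 5 % | 0.63 kg | 0.43 kg |

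If the hazard during the delay is instead held at 1 %, the first column runs from 0.22 to 0.77 kg.

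**2. A real benefit: 4.7 versus 1.3 kg reached by month 6 and held (true difference 3.4 kg).** The carried-forward mean reduces to loss × S(6).
- With 2 % then 6 % in the intervention arm and 4 % in control: 4.7 × 0.8574 − 1.3 × 0.7604 = 4.03 − 0.99 = 3.04 kg. With the beginning-of-pregnancy value it is about 3.2 kg.
- With the 3 % hazards of step 1: 4.7 × 0.9104 − 1.3 × 0.8074 = 4.28 − 1.05 = 3.23 kg.
- The bias now runs against the programme, because each carried baseline costs the intervention arm 4.7 kg and the control arm only 1.3 kg.

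**3. Other paths, with 2 % then 6 % versus 4 %.** Steady loss to 4.7 versus 1.3 kg at month 18 (true difference 3.4 kg) is reported as about 2.1 kg. A loss of 4.7 kg at month 6 regained to 1.3 kg, against a constant 1.3 kg (true difference zero), is reported as about 1.4 kg in favour of the programme.

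**4. Weight-dependent conception.** In simulation with these hazards, raising the hazard by about 6 % per kg lost moved the bias by at most about 0.16 kg. In these illustrations the timing by arm and the carried baselines matter more.

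**5. Effect on the test.** The standard error is 4.5 × √(2/58) = 0.84 kg. A spurious 0.3 kg raises the two-sided 5 % rejection rate to about 6.5 %, and 0.6 kg raises it to about 11 %.

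**The case against.** **Scope.** The method touches only repeated measures. The primary outcome is live birth, and the sample size rests on it. This stands and sets the priority of the point.

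**The qualifier.** The rule depends on the analysis, and a fuller plan may narrow it. That is fair, but the article commits to the method and names no comparison of change that is exempt. Its only stated alternative is the censored time-to-event analysis, which answers another question.

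**Direction.** A reader might infer that the method flatters the programme. The documents do not support a fixed direction. The hazards in step 1 imply conception by month 18 in about 42 % of control and 34 % of intervention women. That is the reverse of the planned live-birth rates (25 versus 50 %) and of the cited pregnancy rates. With the cited weight losses held, the sign reverses.

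**Change of zero.** The protocol measures women at the beginning of pregnancy and does not exclude that value from being carried. In step 1 this reduces the bias without removing it.

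**The visit rule.** The protocol states: "If a woman becomes pregnant within a month of a standard evaluation visit, this visit will be considered as the first pregnancy visit". A reader might infer that it discards a valid pre-conception value. The text does not say whether the visit falls before or after conception, nor that an earlier value replaces it. The rule may only avoid duplicate visits.

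**Dropout.** A reader might infer a large distortion from frozen early losses. The protocol gives 10 % dropout and no difference by arm. With an assumed path of −6, −4, −2 kg, dropout alone gives 0.0333 × (−6) + 0.0333 × (−4) + 0.90 × (−2) = −2.13 kg against −2.0 kg, within a single arm. That is the general weakness of the method and not the main argument.

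**Censoring at pregnancy.** A reader might call this an error. It estimates a cause-specific hazard, which is a recognised target. It would mislead only if read as the probability of reaching a weight outcome.

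**Size.** A bias of 0.4 kg is about half a standard error. This stands for identical paths. The paths in step 3 give more than 1 kg.

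**Conclusion.** The concern holds for the secondary anthropometric and lifestyle outcomes. Followed as written, the rule makes the between-arm comparison depend on conception timing, which the design sets differently in the two arms and which the protocol itself links to weight loss. Neither sign nor size can be fixed from the documents. The illustrations run from a spurious 0.3 to 0.6 kg for the programme under identical paths to a dilution of a sustained 3.4 kg benefit to about 3.0 kg, with larger errors in either direction on other paths. All of them rest on assumed hazards and weight paths. The live-birth analysis and its sample size are untouched. This should be fixed, but it does not threaten the trial's main conclusion.

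**What to change.** 1. Replace last-observation-carried-forward with a mixed model for repeated measures on all measurements up to conception, with arm by visit, baseline value and PCOS stratum.
2. Use the beginning-of-pregnancy measurement as the last pre-pregnancy value where it is valid for that variable, and state how it is placed in time. Waist circumference, for example, is measured only in non-pregnant women. Without this measurement, women who conceive before month 6 contribute no post-baseline value.
3. State that the model estimates change had pregnancy not occurred.
4. Add one sensitivity analysis for dropouts, such as return to baseline or a delta adjustment.
5. Report cumulative incidence with pregnancy as a competing event alongside the censored time-to-event analysis of anthropometric outcomes.

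**Cost:** changed wording and slightly more analysis, with no new data or visits. The model brings a missing-at-random assumption, which conception related to unmeasured weight change could violate. It should be stated openly.

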### Randomisation

An independent statistician will use computerised random number generation to allocate each participant to the intervention or control group. Randomisation will be stratified according to the PCOS or non-PCOS status, based on clinical diagnosis in the patient’s record. Sequences will be generated using permuted block randomisation, with block sizes of two, four or six entries. The allocation sequence will be concealed in corresponding sequentially numbered opaque envelopes. After a participant has completed baseline assessments, the research coordinator will open the envelope to reveal the group allocation to the participant. Participants will be informed of their group assignment at that time.

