### Evaluation of clinical outcomes of the lifestyle program for obese infertile women (Objective 2)

The **primary outcome** will be live-birth rates at 18 months. **Secondary outcomes** will be sub-divided into four categories of clinical outcomes:***Lifestyle and anthropometric outcomes***: evolution of anthropometric measures, changes in lifestyle habits (diet, exercise, sleep, alcohol, and tobacco), physical fitness level, daily energy expenditure from physical activities, time spent in various physical activity intensities, step count, evolution of readiness for change, quality of life.***Fertility outcomes***: pregnancy rate (biochemical pregnancy confirmed by a positive beta-human chorionic gonadotropin (β-hCG) level in the serum), spontaneous abortions, multiple pregnancies, spontaneous vs. ART-induced pregnancy, doses of fertility medications, number of treatment or IVF cycles.***Pregnancy adverse outcomes***: gestational diabetes, hypertension, pre-eclampsia, thromboembolism, caesarean section.***Neonatal outcomes***: birth weight, hypoglycemic episodes, Apgar score, jaundice, admission to neonatal intensive care, congenital defects, intrauterine death.

The results obtained at the CHUS will also be compared to those of women with the same criteria who will be seen in three fertility clinics across Canada. At the CHUS, primary and secondary outcomes will be determined using patients’ assessments, questionnaires and review of patients’ records. At the comparative clinics, charts of patients seen during the same time period will be retrospectively reviewed, and administrative data will be gathered.

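### Randomisation is stratified by PCOS and baselines are measured, but the named between-arm tests use neither: they are valid and give up some precision

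*Protocol article*

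**What the plan says.** Four statements in the protocol article bear on this.

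- **Randomisation:** "Randomisation will be stratified according to the PCOS or non-PCOS status, based on clinical diagnosis in the patient’s record". On the method: "Sequences will be generated using permuted block randomisation, with block sizes of two, four or six entries".
- **Baseline (evaluation section for Objective 2, CHUS only):** "Evaluations of anthropometric measures and lifestyle habits will take place at baseline, prior to randomisation, and then every 6 months for 18 months".
- **Primary outcome (Objective 2):** it "will be live-birth rates at 18 months", a binary outcome with no baseline value.
- **Data analyses and interpretation:** "Univariate analyses will compare the change in a variable in the intervention group with the change in this variable in the control group", with two-tailed unpaired t tests for continuous variables and chi-square or Fisher's exact tests for categorical variables. The section adds: "Multivariate analyses will also be used in order to adjust for baseline differences and for potential confounders". On scale it says: "Continuous variables that are not normally distributed will be log-transformed in order to ascertain normal distribution".

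PCOS appears nowhere in the analysis section. The only factor that the article links to stratified analyses is the weight-loss readiness questionnaire, which is not the randomisation stratum.

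**The concern.** A factor used to stratify allocation is normally carried into the analysis. Stratification makes the arms alike on PCOS, so the true variance of the difference in live-birth rates contains only within-stratum variation. An unstratified chi-square test still counts the between-stratum variation as error. If PCOS predicts live birth, its standard error is too large and the test is slightly conservative.

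The article gives reason to think that PCOS may be prognostic. The BMI threshold for entry differs by PCOS status (27 against 30 kg/m²), and the Background attributes more than 70 % of anovulatory infertility to PCOS.

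For outcomes measured before and after randomisation, subtracting the baseline is less efficient than using it as a covariate, and the result still depends on chance baseline imbalance. At stake is precision in a trial of 128 women. Validity is not in question.

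**Working it through.** **1. The plan's own sample size.** Inputs from the Sample size section: 25 % against 50 %, α = 5 % (taken as two-sided), power 80 %, dropout 10 %. With pooled variance and no continuity correction:

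n = [1.96·√(2·0.375·0.625) + 0.8416·√(0.25·0.75 + 0.5·0.5)]² / 0.25² = (1.342 + 0.557)² / 0.0625 ≈ 57.7, so 58 per group.

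Power at 58 per group is 80.2 %. The total follows as 116 × 1.1 = 127.6, so 128 (dividing by 0.9 gives 129). The stated size therefore matches the unstratified test that the plan names.

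**2. Live birth: variance that the stratum can remove.** The article gives neither the PCOS share nor live-birth rates by stratum, so both are assumed. With half the women having PCOS and an overall rate of 25 %, the within-stratum share of the total variance is:

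- 10-point gap (20 % and 30 %): (0.5·0.20·0.80 + 0.5·0.30·0.70) / (0.25·0.75) = 0.185/0.1875 = 0.987
- 20-point gap (15 % and 35 %): (0.5·0.15·0.85 + 0.5·0.35·0.65) / 0.1875 = 0.947
- 30-point gap (10 % and 40 %): (0.5·0.10·0.90 + 0.5·0.40·0.60) / 0.1875 = 0.88

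The implied type I error of the unstratified test is 2[1 − Φ(1.96/√ratio)]. At 0.947 this is 2[1 − Φ(2.014)] = 4.4 %. At 0.88 it is 2[1 − Φ(2.089)] = 3.7 %.

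**3. Live birth: simulation.** There were 40,000 runs per setting, with arms equal within each stratum, a common odds ratio and overall rates of 25 % and 50 %. Each arm had 58 women (57 at a 70 % PCOS share, because stratum sizes were rounded to even numbers). Chi-square was compared with Cochran-Mantel-Haenszel (CMH), both without continuity correction.

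| PCOS share | Gap in control rates (points) | Type I error, chi-square / CMH | Power, chi-square / CMH |
|---|---|---|---|
| 50 % | 0 | 4.9 % / 4.9 % | 79.7 % / 79.7 % |
| 50 % | 10 | 5.1 % / 5.1 % | 79.9 % / 80.5 % |
| 50 % | 20 | 4.4 % / 4.9 % | 80.7 % / 83.2 % |
| 50 % | 30 | 3.8 % / 5.0 % | 81.8 % / 86.5 % |
| 70 % | 0 | 5.1 % / 5.0 % | 79.9 % / 79.2 % |
| 70 % | 10 | 5.0 % / 5.0 % | 79.9 % / 79.7 % |
| 70 % | 20 | 4.5 % / 4.9 % | 80.8 % / 82.8 % |
| 70 % | 30 | 3.9 % / 4.9 % | 82.0 % / 86.2 % |

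The gain from stratifying runs from −0.7 to +0.6 points at gaps of 0–10, which is essentially none. It is 2.0–2.5 points at a gap of 20 and 4.1–4.7 points at a gap of 30. In every setting the planned test itself stays at about 80 % power or a little above.

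**4. Outcomes with a baseline.** With equal variance σ² at both times and baseline–follow-up correlation ρ, the change score has variance 2σ²(1 − ρ) and ANCOVA has σ²(1 − ρ²). The ratio is 2(1 − ρ)/(1 − ρ²) = 2/(1 + ρ). The article does not give ρ.

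| ρ (assumed) | Variance, change score relative to ANCOVA |
|---|---|
| 0.5 | 1.33 |
| 0.7 | 1.18 |
| 0.8 | 1.11 |
| 0.9 | 1.05 |
| 0.95 | 1.03 |

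The loss is small for a highly stable measure and larger for a less stable one.

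**The case against.** The best defence is that nothing promised is lost. The trial is sized for the test it names, that test does not exceed its nominal level, and a comparison of changes between randomised arms is unbiased. Multivariate analyses are also planned. All of this stands, and it makes the point one of efficiency. It does not remove the point, because the multivariate sentence guarantees neither PCOS nor the baseline value as a covariate.

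A reader might infer three stronger claims. The article does not support them.

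- **That the log rule cannot be followed because weight changes are often negative.** The rule speaks of variables and not of changes. Logging each level and then taking the difference satisfies it for any positive measure. The article does not say that treatment cycles or drug doses, which may be zero, will be logged.
- **That every continuous secondary outcome suffers from the change-score method.** Birth weight, Apgar score, drug doses and cycle counts have no value before randomisation. Nor has live birth, so this part does not touch the primary outcome.
- **That covariates will be chosen after looking at the data.** The sentence on baseline differences could be read that way, but it states no selection rule or trigger. A covariate list is something an article commonly leaves to the full analysis plan.

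**Conclusion.** The point holds as a modest matter of efficiency. The article collects a stratum and baseline values and then names between-arm tests that use neither as a stratum or covariate. There is no bias, no inflated type I error and no error in the sample size from this source.

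For live birth, the cost ranges from nothing to about 5 points of power. It depends on how far the PCOS strata differ, and the article does not say. For repeated continuous measures, the excess variance is 3 % to 33 % for ρ between 0.95 and 0.5. These sizes rest on the assumed PCOS share, gap and ρ, on equal variances over time, and on a common odds ratio across strata. The change is worth making because it costs nothing, even though the trial would remain interpretable without it.

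**What to change.** Change the analysis wording as follows, before outcome data by arm are examined:

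1. **Live birth:** make the primary comparison a Mantel-Haenszel test with a risk difference, stratified by PCOS status as used at randomisation. If logistic regression with PCOS is preferred, expect any gain in power and not in a smaller standard error of the log odds ratio.
2. **Outcomes with a pre-randomisation value:** use ANCOVA, or a mixed model for repeated visits, of the follow-up value with baseline value and PCOS as covariates. This replaces the t test on change.
3. **Log scale:** where it is needed, log the follow-up and baseline levels and never the change. One sentence settles how the present rule is to be read.

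The cost is wording only. No extra women, visits or measurements are needed, and the sample size stands.
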